#### Concealment mechanism {16b}

An independent researcher, not involved in the experiment, will follow the computer-generated random sequence results to insert the assignment codes into sequentially numbered, sealed, opaque envelopes, thereby obfuscating group allocation. As per the experimental design, once opened according to the stipulated procedures, participants will be assigned to either the “control group” or “trial group” based on the corresponding “0” or “1” on the random number card.

#### Implementation {16c}

During the recruitment phase, participants will be evaluated by a physical therapist who is not involved in the randomization process. Following this evaluation, sealed and opaque envelopes will be opened on-site to ascertain the assignment group, with participants thereafter being allocated to the respective groups in a 1:1 ratio. To ensure a balanced distribution among the groups, permuted blocks of size 4 will be employed randomly.

### Blinding

#### Who will be blinded {17a}

Blinding of volunteers and doctors to group assignments is unfeasible. The decision not to blind the assessors is made given that the subjects are not blinded and the outcomes are self-reported. Although participants, doctors, and assessors are not blinded, alternative methods are employed to minimize bias. Specifically, participants and assessors are not informed of the trial hypothesis to mitigate the risk of bias stemming from unblinding.

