### Interventions

Qualified physiotherapists will provide treatment to participants in both groups but will not be involved in assessing and evaluating the outcome measures. The physiotherapy interventions for both groups will span 12 weeks, adhering to the recommendations from the 2019 guidelines established by the American Rheumatoid Arthritis Foundation [20]. Participants will be motivated to fully partake in the intervention and assessment processes throughout the trial. The physiotherapist administering the treatment will document details regarding participation rates, medication changes, and any adverse events during and after the treatment in the daily case report form.

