### CG Therapy

The intervention in the control group includes app-based patient education and topical use of NSAIDs, diclofenac diethylamine latex. Patients in the control group will be informed that they can receive TG therapy after the 12-week trial is over.

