##### Walking ability test

The time up go test (TUG) is a quick assessment of functional walking ability [28]. At the time of assessment, the patient will be seated in a backrest chair with armrests (seat height approximately 45 cm, armrest height approximately 20 cm), with the body resting on the back of the chair and hands resting on the armrests. If using a walker such as a cane, place your hand on the walker. Paste colored strips or draw a clearly visible thick line or place an obvious mark on the ground 3 m away from the seat. After the tester gives the “go” command, the patient stands up from the back of the chair, stands on his or her footing, walks forward 3 m with the usual walking gait, passes the thick line or mark, turns around, walks back to the chair, and then turns and sits down, leaning against the back of the chair. During testing, no help can be provided. The tester records the time in seconds for the patient to stand up from the starting position (reclining) and sit down again and lean back. The patient may be asked to practice several times to understand the content of the test before the formal test. In addition, the patient’s risk of falling during the test period will be determined. The time criteria are < 10 s, free movement; < 20 s, most can move independently; 20–29 s, unstable movement; and > 30 s, dyskinesia. The risk criteria are as follows: 1 for normal, 2 for very slight abnormalities, 3 for mild abnormalities, 4 for moderate abnormalities, and 5 for severe abnormalities [29].

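### The self-report reason given for leaving assessors unblinded does not fit the Timed Up and Go, which a tester times, so this secondary outcome carries observer bias that could be reduced

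*Protocol article*

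**What the plan says.** **Blinding.** The section on who will be blinded ({17a}) describes blinding as unfeasible for volunteers and doctors. For assessors it reports a choice: "The decision not to blind the assessors is made given that the subjects are not blinded and the outcomes are self-reported". The mitigation offered is that "participants and assessors are not informed of the trial hypothesis to mitigate the risk of bias stemming from unblinding".

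**TUG.** The section on the walking ability test describes an observed test. It starts "After the tester gives the “go” command", and "The tester records the time in seconds for the patient to stand up from the starting position (reclining) and sit down again and lean back". Practice beforehand is allowed, with no set number of attempts. Fall risk during the test is also determined, on a five-point scale that runs from normal at 1 to severely abnormal at 5. The rater is not named.

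**Schedule.** Table 2 (Outcome measures {12}) places TUG under physical function at baseline and at 4, 8 and 12 weeks. Its reporting method is walking ability. WOMAC, in the same domain, is marked as self-reported.

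**Staff and records.** Under Interventions, the physiotherapists "will provide treatment to participants in both groups but will not be involved in assessing and evaluating the outcome measures". They do record participation and medication changes in the daily case report form. Under Data management {19}, outcome assessors document all procedures and data in the case report forms. Access is limited to them and the corresponding author.

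**The concern.** A justification that holds for the questionnaires has been applied to every outcome. When the patient fills in a scale, masking the person who hands it over gains little. When a tester holds the stopwatch, decides how much practice to allow and probably grades the gait, knowledge of the arm has a direct route into the recorded value.

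The protocol's own aims make this relevant. The abstract and introduction criticise telemedicine research for lacking objective evaluation and for relying on questionnaires that may introduce bias. TUG is the one functional outcome here that does not rest on the patient's opinion, and it supports the first secondary objective. The statistical methods section also plans an effect size for every outcome, to be interpreted against Cohen's boundaries. A systematic tester effect would pass straight into that interpretation.

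The limitations in the Discussion mention that patients and physical therapists cannot be blinded. They do not mention assessors or TUG.

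**Working it through.** No figure in the plan depends on this point, so the check is a comparison of the sections.

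1. **Is TUG self-reported?** No. Table 2 does not label it so, and the walking ability section says "The tester records the time in seconds for the patient to stand up from the starting position". Under section {18a}, the assessor fills out the examination forms and the patient completes the questionnaires. The second ground in {17a} is therefore untrue for TUG.

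2. **Does the first ground, unblinded subjects, cover TUG?** In part. An informed patient can tell the tester the arm, and can walk differently because of knowing it. Neither makes it pointless to keep the arm from the tester where that is possible.

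3. **Which parts are exposed to the observer?** There are three:
   - The start and stop of the timing, which is fairly objective.
   - The amount of practice, which is not fixed and so can differ between patients and arms.
   - The 1 to 5 rating, which is a judgement. The text does not say who makes it. The tester is the natural reading, but this is an inference.

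4. **Is TUG the only performance-based functional outcome?** Yes, on Table 2. WOMAC is self-reported. Movement completion rate is captured by the device and measures adherence, not function.

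5. **Is masking the tester excluded by the plan?** No. Infeasibility is claimed for volunteers and doctors only, and treating physiotherapists are already kept out of assessment.

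6. **Can the present assessors simply be declared masked?** No. As {19} stands, they work with case report forms, and the records described under Interventions can reveal the arm. The exercise adherence scale can reveal it too, because the exercise module is closed to controls. Masking needs a separate TUG form and TUG placed first at the visit.

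7. **How large is the bias?** It cannot be computed. The protocol gives no standard deviation for TUG and no information on timing error by arm.

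8. **Does it reach the primary outcome?** No. The patient marks the VAS line.

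**The case against.** **The strongest case for the plan.** The trial is declared open-label, its assessors are openly unblinded, and {17a} gives two grounds, the first of which bears on TUG. The patient performs the walk, so expectation can affect it whoever holds the stopwatch. Assessors receive uniform training and are not told the hypothesis. TUG is one of several secondary outcomes. All of this stands, and it limits the weight of the point. It does not make the self-report ground true for TUG, and keeping the hypothesis from assessors does not hide the allocation from them.

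**Stronger readings that the documents do not support.**

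- *Hypothesis masking is worthless.* A reader might infer this because participants receive written information on the study's aims (Consent {26a}), and because of this sentence: "Patients in the control group will be informed that they can receive TG therapy after the 12-week trial is over". Both facts concern participants. Neither shows that assessors know the hypothesis, and observer bias in TUG is about assessors. Being told a study's aims is also not the same as being told a directional hypothesis.
- *The bias is as large as a small or medium effect.* Such a figure would need an assumed standard deviation divided into an assumed timing error. Neither number is in the documents.
- *Masking makes TUG free of bias.* It does not, because patient effort and disclosure remain.
- *Masking is almost free.* The separation of treating staff shows that assessors distinct from them are planned. It does not show a dedicated TUG tester, and the case report form arrangements must change.

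**Conclusion.** The point holds in a limited form. The self-report reason in {17a} is factually wrong for TUG, and for that outcome the plan accepts an observer bias that it could reduce. It concerns one secondary outcome, the only performance-based measure of function, at the assessments made after allocation is known. The practice runs and the 1 to 5 rating are more exposed than the timing.

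Masking would remove only the observer's part of the bias, whose size the documents do not allow anyone to compute. The primary VAS result and the sample size are untouched.

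Two assumptions support this conclusion. One is that the tester makes the 1 to 5 rating. The other is that an assessor can be kept from the arm-revealing records, which nothing in the article rules out but which its current form handling does not provide for.

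**What to change.** 1. Have TUG done by an existing assessor who is not told the allocation, before any other assessment at the visit.
2. Record the time and the 1 to 5 rating on a separate TUG form, and state who makes the rating. That assessor should not have access to the case report form entries that reveal the arm. Sections {19} and Interventions need matching wording.
3. Ask patients not to disclose their group, and use the same script and the same fixed number of practice runs in both arms.
4. Correct {17a} to say that TUG is an exception to the self-reported outcomes.
5. If masking fails or proves impracticable, report TUG as open to observer bias and add this to the limitations.

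The cost is some form handling and scheduling, with occasional unmasking by patients. The sample size and the analysis model do not change.

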### Interventions

Qualified physiotherapists will provide treatment to participants in both groups but will not be involved in assessing and evaluating the outcome measures. The physiotherapy interventions for both groups will span 12 weeks, adhering to the recommendations from the 2019 guidelines established by the American Rheumatoid Arthritis Foundation [20]. Participants will be motivated to fully partake in the intervention and assessment processes throughout the trial. The physiotherapist administering the treatment will document details regarding participation rates, medication changes, and any adverse events during and after the treatment in the daily case report form.

### The explanation for the choice of comparators {6b}

Patients in the control group will receive usual care rehabilitation treatment, with app-based patient education (10 min per day, 1 day per week, for 12 weeks) and topical use of NSAIDs, diclofenac diethylamine latex (4 times a day, 7 days per week, for 2 weeks).

### Intervention description {11a}

#### TG therapy

The intervention measures for the trial group include app-based exercise therapy, patient education, and WeChat video-based health coaching.

#### App-based exercise therapy

The individuals will be given instructions by the researchers on how to download, sign up for, and utilize the app throughout the first diagnosis and therapy. In order to associate and bond with the doctor or therapist, patients must affirm that they have read the informed permission form, complete the personal information and questionnaire honestly, and then input the activation code. The patient can perform the training under the direction of the action video when the doctor approves the workout prescription. Based on the patient's age, gender, body mass index (BMI), lesion site, and degree, a personalized treatment strategy is adopted, with a focus primarily on quadriceps muscle training and neuromuscular training modules. According to the patient's preferences and practicality, the doctor or physical therapist chooses the most appropriate exercise for the patient to prescribe. The action training video, the frequency, the intensity, the length, and the overall quantity of exercise are all included in the prescription's fundamental material. Pictures, audio prompts, and wearable device monitoring are all integrated in the video instructions for the training exercises. The wearable device is equipped with Inertial Measurement Units (IMUs), which capture the acceleration, angular velocity, and orientation of the body part to which they are attached. This device is non-invasive and does not necessitate direct attachment to the skin. We are committed to enhancing the convenience and comfort for users when employing this device in their daily routines and will seek official medical device approval prior to public release. By capturing motion features, wearable device monitoring can record a patient's individual joint and determine whether the patient has completed the task. In addition, a deep learning system based on a large language model can describe the actions the patient is doing through changes in the node position, such as “this patient is extending his lower limbs in a standing position.” The number of movements, estimated length, movement preview, and written version of the movement instructions may all be seen prior to the activity beginning (shown in Fig. 2). You can start working out after successfully connecting to the wearable device after wearing it properly. The system will alert the patients that the standard has been attained when the exercise reaches the upper or lower limit of the intended duration, at which point they can decide whether to continue exercising or stop. The patients will be urged to meet the standard after the exercise, and they will be asked to rate their level of felt exertion. Based on patient input, the doctor will modify the recommended workout regimen. Through the alarm in the app, patients could set exercise time according to their own schedule for three times each week for 12 weeks, for a total of 36 training sessions. The software allows therapists to create staged goals in advance and remind patients on a regular basis whether they have achieved their goals or not.

**Fig. 2 Fig2:**
[figure not shown]
Examples of app content

The training moves are as follows:

Quadriceps exercises are designed to improve knee stability by increasing endurance and strength in major muscle groups. The therapist will make an exercise plan for the patient in advance according to the baseline measurement results, and import the training actions into the movement library of the app. According to the literature [21], the movements of training include (i) knee extension in a fixed range, (ii) sit and extend the knee, (iii) maintain the knee extension at 30° in the sitting position, (iv) straight leg elevation training, and (v) sitting elastic belt training.

Neuromuscular training aims to improve sensorimotor control to promote functional stability of the knee. According to the previous literature, the actions are as follows [22]: (i) core stability/postural function — static hip bridge with the help of a yoga ball; (ii) postural positioning — gliding forward and backward with the help of a horizontal bar or handrail standing position; (iii) lower limb muscle strength — knee flexion and extension muscle training in the sitting position with the help of an elastic band; (iv) functional exercise — stand and sit up training and up and down steps exercise.

Two to three sets of 10–15 repetitions will be performed for each exercise, with a 10–15-s rest before continuing to the next set of exercises. Subjects will be required to follow the app to complete the training sessions, 30 to 40 min each time, 3 times a week for 12 weeks, with a total of 36 training sessions.

### App-based patient education

During the baseline assessment, physical therapists will present patients with animated educational videos concerning knee osteoarthritis. Following this, patients will be directed to read through 12 illustrated educational articles on KOA on a weekly basis via an app [23]. Each article is estimated to require between 10 to 20 min to read through. It covers terms like definition, etiology, pathogenesis, diagnosis, treatment, day-to-day management, how to stop knee osteoarthritis from progressing and recurring, food management, weight management, and other topics. The questionnaire connected to knowledge of knee osteoarthritis will be provided through the app once every Friday in order to determine whether the patients actually read the information about the condition that was promoted by the app. The results of the questionnaire will be used to evaluate the patient’s learning situation.

### CG Therapy

The intervention in the control group includes app-based patient education and topical use of NSAIDs, diclofenac diethylamine latex. Patients in the control group will be informed that they can receive TG therapy after the 12-week trial is over.

### App-based patient education

The treatment content is the same as that of the trial group. The app could set open permissions for patients, and the patients in the control group could only receive patient education knowledge once a week for 12 consecutive weeks, a total of 12 times. The exercise training plate is not open to it.

#### Drug therapy

Diclofenac diethylamine latex (GSK Consumer Healthcare S.A. Production, 20 g/piece, batch number DV6D) for external use, apply four times a day, respectively along the front of the affected area, inside and outside the order, gently rub to promote the absorption of the drug. The range of administration should be greater than 10 mm at the distal end of the knee joint. Patients should be instructed to avoid contact with clothing within 10 min of medication and avoid bathing or exercising within 1 h after medication and continue medication for 2 weeks [24].

### Criteria for discontinuing or modifying allocated interventions {11b}

Should a participant opt to withdraw from the trial prematurely, the physiotherapist will promptly reach out to ascertain the reason for their withdrawal. Participants who exit the trial, become unreachable for over 2 weeks, and fail to complete the outcome evaluation will be categorized as dropouts [25].

i)Patients desiring to cease participation;ii)Patients unable to undergo the baseline assessment;iii)Patients failing to complete the app-based exercise therapy sessions; iv)Patients experiencing exacerbated symptoms.

### Strategies to improve adherence to interventions {11c}

To improve the patient’s adherence to the intervention protocols, we will use wearable device, through the change in joint angle, wearable device monitoring may record the patient's individual joints and determine if the patient has finished the task. Furthermore, once a week, a group WeChat video will be held. Health coaching based on group video can enable patients to provide peer aid and psychological support and improve therapist-patient adhesion.

### Relevant concomitant care permitted or prohibited during the trial {11d}

All participants will be provided with the same version of the app, which will remain unchanged throughout the trial. During the treatment phase, should a participant's condition deteriorate, they are permitted to utilize any relevant treatment to manage the disease, such as drug therapy or physical factor therapy, among others. However, engaging in additional exercise therapy is prohibited. Participants are required to report any such additional treatments accurately to the investigator, who will then document these in the case report forms.

### Outcome measures {12}

After obtaining informed consent, a baseline assessment will be conducted. The details gathered include participants’age (acquired using the birthdate shown on their ID cards), gender, height, weight, BMI, education level, occupation, income source, hobbies, interests, marital status, smoking and alcohol use, medical history, knee pain duration, pain severity (current, worst, mildest), triggers, alleviating factors, and pain-avoiding behaviors. The primary and secondary outcomes will be evaluated before commencing the trial (baseline) and at 4-, 8- and 12-week post-intervention (shown in Table 2). We focus on changes in outcomes at 12 weeks after treatment.

**Table 2 Tab2:** Overview of the measurements and timing of measurements

Domain	Reporting methods	Questionnaire line	Base	4 weeks	8 weeks	12 weeks
Demographic characteristics	Self-reported	Purpose built	√	-	-	-
Pain intensity	Self-reported	VAS	√	√	√	√
Physical function	Self-reported	WOMAC	√	√	√	√
	Walking ability	TUG	√	√	√	√
Quality of life	Self-reported	SF-36	√	√	√	√
Self-efficacy	Self-reported	PSEQ	√	√	√	√
Mental health status	Self-reported	DASS21	√	√	√	√
Fear-avoidance in exercise	Self-reported	TSK	√	√	√	√
Pain catastrophic imagery	Self-reported	PCS	√	√	√	√
Exercise adherence	Self-reported	EARS	-	√	√	√
	Events	Movement completion rate	-	√	√	√
Adeverse events	Self-reported	-	-	√	√	√

#### Primary outcome measure

##### Pain intensity

A visual analog scale (VAS) is used to evaluate knee pain. Patients will be asked to rate their current pain level on a line of 100 mm in length, with 0 representing no pain and 100 representing extreme pain, and patients mark this point on the current pain line. The VAS score is then determined by measuring in millimeters from the left end of the line to the point marked by the patient. Patients can experience pain ranging from no pain to extreme pain. Scores range from 0 to 100, with higher scores indicating more severe pain [26].

